### Data management {19}

Data collection and management will follow the German General Data Protection Regulation. Data is only collected by members of the Department of Medical Psychology | Neuropsychology and Gender Studies. All paper-based data (e.g., informed consent, neuropsychological assessment data, scoring sheets) are stored in locked cabinets at the Department of Medical Psychology | Neuropsychology and Gender Studies in a room with restricted access. Data will be sorted by pseudonymized study ID for easy access during the duration of the study (details on the pseudonymization process are described in Sect. “Confidentiality {27}”). Data acquired on paper will be digitalized by blinded research fellows and student assistants from the study team using SPSS Statistics 29 (IBM Corp., Armonk, NY, USA). SPSS data entry and management is conducted via a dual-control principle according to pre-specified standard operating procedures and is performed continuously during study progress. Each individual step (i.e., data collection and evaluation, digitalization, and monitoring) is documented. The database is saved to a secure server of the Department of Medical Psychology | Neuropsychology and Gender Studies, accessible only through a password-protected computer to members of the study team. Backups are performed regularly. Informed consent forms are stored separately from all other paper-based data in a locked cabinet with restricted access. Digitally acquired data during assessments, i.e., MDS-UPDRS-III videos, are recorded using a standard video camera. Videos are continuously transferred to, saved, and backed up to a password-protected computer and an external encrypted hard drive with restricted access. Scoring of these data is performed by a blinded student assistant not otherwise involved in the study. The scored data is then transferred into the overall SPSS database used for this study. Digitally acquired CT data are stored via the CT program on an external server, inaccessible to members of the study team. Therefore, pseudonymized CT performance data is requested regularly from HelferApp GmbH, Gommern, Germany. Data is saved and stored in a separate data file on a password-protected computer as well as an encrypted hard drive accessible only to one member of the study team (author [name]) and is backed up regularly. Following good scientific practice, all data will be archived and made available upon request for at least 10 years after study completion. No data monitoring committee is used for this study.

### Confidentiality {27}

All collected data (except the informed consent) will be pseudonymized by assigning a unique, randomly generated, nonconsecutive personal identification number (study ID) to each participant. The study IDs have the following format: TPA-XXX (e.g., TPA-123). The ID numbers were generated using an online random number generator. All paper-based and digital data (i.e., neuropsychological assessment data, scoring sheets, MDS-UPDRS-III videos, and CT performance data) are encrypted and referenced using the personal study ID. Any information that might allow identification of a participant (e.g., personal information on medication plans) is made unreadable (i.e., blackened out) to ensure pseudonymization of participant data. A single list (key list) is kept for the duration of the study, linking participants’ names to their personal study ID. This key list is securely stored, saved, and regularly backed up on a password-protected computer and an external encrypted hard drive only accessible to one member of the study team (author [name]). The key list will be deleted after study completion. Following deletion, all study-relevant data will be anonymous. Further information on data management and storage is described in the previous paragraph (Sect. “Data management {19}”). No participant identification details will be reported in publications.

### Plans for collection, laboratory evaluation, and storage of biological specimens for genetic or molecular analysis in this trial/future use {33}

For this study, no biological specimens are collected or analyzed. Therefore, no plans for collection, laboratory evaluation, and storage of such data are needed.

## Statistical methods

### Statistical methods for primary and secondary outcomes {20a}

The primary analysis is according to the intention to treat, with no exclusions. The change from baseline in the primary outcome MoCA is analyzed by a linear mixed model for repeated measures (MMRM) with fixed effects for baseline, group, time, and group × time interaction (ARH1-structured variance–covariance matrix over time). The primary comparison at T1 (week 9) is based on a pairwise contrast of estimated marginal means with a 95% confidence interval. Secondary outcomes (i.e., further timepoints and measures) are analyzed along the same line, however from an exploratory viewpoint only; thus, no multiplicity adjustment is required. Where available, observed changes will also be interpreted in relation to published minimally clinically important differences (MCIDs) to evaluate clinical relevance in addition to statistical significance.

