### Sample size {14}

The a-priori sample size calculation conducted in G*Power 3.1 was based on a meta-analysis [29] reporting a small efficacy of CT on overall cognitive functions. Based on this result, a small effect size is expected for global cognitive functions (*d* ≥ 0.3–0.5). With a power of 80% and a significance level of *p* = 0.05, *n* = 64 participants should be included in each of the two groups. Considering a dropout rate of 10% [38, 44], the sample calculation provided an overall sample size of *n* = 140 participants with each *n* = 70 persons randomized to either EG or CG.

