## Assignment of interventions: allocation

### Sequence generation {16a}

The allocation sequence was computer-generated with the help of a statistician (author [name]) using the website www.randomization.com. Allocation follows a stratified randomization procedure with permuted blocks of variable length. Participants are stratified by age (< 65 years vs. ≥ 65 years) and cognitive baseline level (*MoCA* ≤ 26 points vs. > 26 points).

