### Methods for additional analyses (e.g., subgroup analyses) {20b}

Predictiveness of change in the main outcome and secondary outcomes regarding baseline, age, sex, education, disease-related factors (e.g., severity of motor symptoms), and (neuro)psychological factors (e.g., cognitive baseline level, self-efficacy, and depressive symptoms) is explored by adding both main effects and interactions with group to the model equation. Moreover, models are fitted in corresponding subgroups.

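### The primary model leaves out age, one of the two stratification factors; if age is prognostic for MoCA change, the standard error is modestly overstated and the test conservative.

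*Protocol article*

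**What the plan says.** Sequence generation {16a}: "Allocation follows a stratified randomization procedure with permuted blocks of variable length". The two factors are named there: "Participants are stratified by age (< 65 years vs. ≥ 65 years) and cognitive baseline level". The age cut is at 65 years; the cognitive cut is a MoCA of up to 26 versus above 26.

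Statistical methods {20a}: the change from baseline in MoCA is analysed by an MMRM with "fixed effects for baseline, group, time, and group × time interaction". The covariance structure and the primary contrast are given in the same place, so the list reads as the complete mean model.

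Methods for additional analyses {20b}: age appears here, in an exploratory role. "Predictiveness of change in the main outcome and secondary outcomes regarding baseline, age, sex, education, disease-related factors" and further factors "is explored by adding both main effects and interactions with group to the model equation".

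Sample size {14}: "a small effect size is expected for global cognitive functions (*d* ≥ 0.3–0.5"), and "With a power of 80% and a significance level of *p* = 0.05, *n* = 64 participants should be included in each of the two groups". With 10% dropout the total is 140.

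**The concern.** Stratified blocks hold the age mix nearly equal in the two arms, so age differences contribute almost nothing to the sampling variation of the treatment estimate. A model without age does not know this. It leaves the age-related variance in the residual and computes the standard error as if the age mix could still differ by chance between arms. If age matters for the outcome, the confidence interval is wider than the design warrants, the test rejects less often than 5% under the null, and some power is given away.

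The analysis also does not match the design. The sponsor chose only two factors to balance. The model uses one of them, in the more efficient continuous form, and drops the other.

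**Working it through.** **1. Is age really absent?** The word baseline in the {20a} list could be stretched to mean baseline characteristics in general. Section {20b} rules that out: it names baseline and age as separate items and speaks of adding them to the model equation. The base equation therefore has no age term.

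**2. The plan's own sample size.** A two-sample t-test, two-sided alpha 0.05, 80% power and d = 0.5 gives 64 per group (power 80.15%), as stated. The same test at d = 0.3 would need 176 per group, so the stated figure belongs to the upper end of the range. After 10% dropout, 140 × 0.90 = 126, or 63 per arm; this is used below.

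**3. Formulas.** Let R² be the share of the residual variance in MoCA change, given baseline MoCA, that the age stratum explains. The documents give no value, so it is an assumption, shown from 0 to 10%. With age balanced by design:

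- SE without age ÷ SE with age = 1/√(1 − R²)
- true size without age = 2 × [1 − Φ(1.96/√(1 − R²))]
- z = 0.5/√(2/63) = 2.806
- power without age = Φ((z − 1.96)/√(1 − R²))
- power with age = Φ(z/√(1 − R²) − 1.96)

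Worked for R² = 5%: √0.95 = 0.9747. SE ratio 1/0.9747 = 1.026. Size 2 × [1 − Φ(2.011)] = 4.4%. Power without age Φ(0.846/0.9747) = 80.7%; with age Φ(2.879 − 1.96) = 82.1%.

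| Assumed R² | SE overstated by | True size of 5% test | Power without age | Power with age | Gain (points) |
|---|---|---|---|---|---|
| 0 | 0% | 5.0% | 80.1% | 80.1% | 0 |
| 2% | 1.0% | 4.8% | 80.4% | 80.9% | 0.5 |
| 5% | 2.6% | 4.4% | 80.7% | 82.1% | 1.4 |
| 10% | 5.4% | 3.9% | 81.4% | 84.1% | 2.7 |

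**4. What these R² values mean.** If the two age groups were of equal size (assumption), R² = 0.25 × Δ², where Δ is the difference between them in residual SDs. R² of 2%, 5% and 10% then correspond to Δ = 0.28, 0.45 and 0.63. The last exceeds the treatment effect that the trial is powered for.

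**5. Simulation.** 128 participants, 2 × 2 strata, blocks of 4 and 6, ANCOVA at one time point, residual SD 1, 6,000 runs per setting. SE, spread and size are from the runs with no treatment effect; power is from those with d = 0.5.

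| R² | Mean model SE, without / with age | True spread of estimate, without / with age | Size, without / with age | Power, without / with age |
|---|---|---|---|---|
| 0 | 0.176 / 0.177 | 0.175 / 0.175 | 4.5% / 4.5% | 79.6% / 79.4% |
| 2% | 0.177 / 0.175 | 0.176 / 0.176 | 4.9% / 5.0% | 81.0% / 81.5% |
| 5% | 0.177 / 0.172 | 0.173 / 0.173 | 4.3% / 4.9% | 79.9% / 81.4% |
| 10% | 0.177 / 0.168 | 0.170 / 0.170 | 4.5% / 5.4% | 81.1% / 83.6% |

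The spread of the estimate is practically the same with and without age; only the reported SE differs. The Monte Carlo error of a simulated size near 5% is about √(0.05 × 0.95/6000) = 0.28 points. At R² = 10% the simulated size without age (4.5%) lies nearer to 5% than the formula's 3.9%. The formula assumes perfect balance, which incomplete blocks do not quite give, so the formula figures for size are best read as the outer edge.

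**The case against.** The strongest objection is that nothing in the documents shows age to be prognostic here. The Discussion calls earlier findings on age as a predictor of training response inconclusive. That is about response to training rather than about prognosis, but no other statement in the documents fills the gap. This stands: a reader might infer that the standard error is too large as a matter of fact, and the documents do not support that. At R² = 0 there is no overstatement, and 10% needs a large age difference in a change over a few weeks.

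It is also fair that the error is small and on the safe side, that the cognitive factor is already covered by baseline MoCA, and that age will enter the model in the exploratory analyses of {20b}. Those analyses do not supply the primary confidence interval or test, so they do not replace adjustment there.

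A reader might also link this to the trial's power. The link is weak. With 64 per group and d = 0.3, power is 39.1%, and it reaches only 42.7% with age included at R² = 10%. The spread of effect sizes in {14} is a separate matter, and an age term does not cure it. The sample size calculation also takes no explicit credit for adjustment for baseline MoCA.

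The absence of a baseline-by-time term might be read as a second fault. With randomised groups balanced on baseline MoCA, a common baseline slope does not bias the primary contrast. No size has been shown for any loss, so this remains a modelling preference.

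Finally, the article condenses a longer plan that is not shown. This carries little weight, because the article sets out the model terms explicitly and does not defer them.

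**Conclusion.** The omission is real and visible in the article: age is a stratification factor and the stated primary model does not contain it. The consequence is conditional and modest. Over an assumed R² of 0 to 10%, the standard error is overstated by 0% to 5.4%, the true size falls from 5.0% to no lower than about 3.9%, and between 0 and 2.7 points of power at d = 0.5 are lost. The primary analysis remains valid: no bias, no inflated type I error. The figures rest on near-perfect balance of age within blocks and on a normal approximation with 63 per arm. The case for the change does not depend on a large R². If age is not prognostic, including it costs practically nothing (simulated SE 0.177 against 0.176); if it is, the reported precision comes into line with the design.

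**What to change.** Add the age stratum as randomised (under 65 versus 65 and over) as a fixed effect to the primary MMRM, beside baseline MoCA, group, time and group by time. Name this single form; leaving open a choice between stratum and continuous age would weaken the pre-specification. Carry the same term into the imputation model of the reference-based sensitivity analysis in {20c}, so that it stays consistent with the primary model.

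Fix the change in writing before any unblinded analysis, since a covariate added later could look chosen from the data. The cost is one degree of freedom and a sentence in the analysis plan; age is already collected at baseline.

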### Objectives {7}

Based on a hybrid type 1 clinical trial design [54], this study has three objectives. The first is to assess the short- and long-term effects of a 5-week digital CT intervention (“HeadApp/NEUROvitalis Digital” [55]) in people with advanced PD on global cognitive functions, with the Montréal Cognitive Assessment (MoCA) [56] as the primary outcome, and other cognitive, motor, and (neuro)psychological variables as secondary outcomes (e.g., specific cognitive functions, depressive symptoms, and severity of motor symptoms). It is expected that CT will improve global cognition and other cognitive and noncognitive functions, both in the short term and over a 3-month follow-up period. The second objective is to examine the feasibility and acceptability of the CT. Specifically, it is hypothesized that the CT intervention is feasible in terms of adherence to the training schedule, completion of training days, and technical handling and is acceptable in terms of participant motivation, satisfaction, and integration of CT into daily life. Finally, the study seeks to explore and identify possible predictors of CT responsiveness, including sociodemographic factors (e.g., age, sex, education), motor (e.g., severity of motor symptoms), and cognitive and (neuro)psychological factors (e.g., cognitive baseline level, self-efficacy, and depressive symptoms).

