### Outcomes {12}

Based on a hybrid type 1 clinical trial design [54], our primary objective is to evaluate the efficacy of the CT. The primary outcome measure is overall cognitive function assessed by the German version of the MoCA [56, 69]. Secondary outcomes include specific cognitive functions, motor, and neuropsychiatric symptoms. Additionally, further patient-reported non-motor outcomes including QoL and ADL were defined. Non-cognitive outcome measures were selected based on recommendations of the International Parkinson and Movement Disorder Society (MDS) and the current German Society of Neurology guideline [70, 71]. CT feasibility and acceptability are also assessed as secondary outcomes. An overview of all outcome measures is shown in Table 2. A more detailed description of the outcome assessment and collection follows in Sect. “Plans for assessment and collection of outcomes {18a}”

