While the study has many strengths in place for the prevention or handling of potential challenges, certain limitations must still be acknowledged. First, since the study involves digital CT, participants must have access to a digital device with a reliable Internet connection and must be capable of using such a device to complete CT. This requirement may exclude some individuals with advanced PD, despite their eligibility based on disease stage. However, an advantage of the digital CT format is that it allows participation from individuals across Germany, including those who are immobile or unable to travel to the research facility. Second, the advanced PD stage may introduce additional challenges. These include disease-related complications, complex medical treatments, fluctuations of motor and non-motor symptoms—potentially affecting the ability to complete CT—and other complications that could impact the study’s progress or lead to a higher-than-expected dropout rate. Moreover, the complexity of care of people with advanced PD may lead to a higher rate of protocol deviations, which must be accounted for. Third, while this study aims to examine a participant pool that more accurately reflects clinical practice, it still excludes individuals with PD who are already suffering from dementia, thus precluding any conclusions on CT in people with PDD. Future research will need to build on this study’s findings to include and investigate individuals with PDD.

Fourth, since participants receive CT together with psychoeducational videos, any observed CT effects must be interpreted as resulting from the combined intervention, as the current study design does not permit separating the effects of CT from those of the psychoeducational component. Further studies using more elaborate statistical designs are needed to isolate specific contributions of each component.

In conclusion, the current study is, to the best of our knowledge, the first large-cohort study examining the effects of CT on people with PD in more advanced disease stages, thus offering class I evidence on the efficacy of digital CT in PD. CT could be an easy-to-administer, far-reaching, and safe intervention to strengthen cognitive functions in this patient group and prevent cognitive decline.

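### The 3-month MoCA hypothesis has no alpha-controlled test, although a fixed sequence after T1 would supply one at no cost to the primary test

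*Protocol article*

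**What the plan says.** Objectives {7} of the protocol article introduce the efficacy aim thus: "The first is to assess the short- and long-term effects of a 5-week digital CT intervention". The same sentence names the MoCA as primary outcome for global cognition. The expectation that follows is directional and covers both horizons: "both in the short term and over a 3-month follow-up period".

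Outcomes {12} gives no timepoint for the primary outcome: "The primary outcome measure is overall cognitive function assessed by the German version of the MoCA".

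The timepoint first appears in Statistical methods {20a}: "The primary comparison at T1 (week 9) is based on a pairwise contrast of estimated marginal means with a 95% confidence interval". On everything else that section says "Secondary outcomes (i.e., further timepoints and measures) are analyzed along the same line, however from an exploratory viewpoint only", and it concludes: "thus, no multiplicity adjustment is required". No order of testing is given.

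The Discussion describes the 3-month data as allowing sustained and delayed benefit to be explored.

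**The concern.** The MoCA at 3 months is the primary outcome measure under a stated directional hypothesis, yet {20a} gives it the same standing as any secondary scale at any visit. A reader of {7} and {12} alone cannot tell that only T1 is confirmatory. {7} uses the language of exploration for the predictor objective but not for the long-term effect.

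What is at stake is the standing of a positive 3-month result. The abstract gives the scarcity of long-term data as part of the rationale. Under the plan as written, even a clear MoCA difference at T2 could be reported only as an exploratory observation. The measurement and the model needed for a stronger statement are already in the plan.

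**Working it through.** **1. The plan's own sample size.** Inputs from Sample size {14}: power 80%, significance level 0.05, d in the range 0.3-0.5, dropout 10%. Sidedness is not stated.
- Two-sample t-test, two-sided 0.05, d = 0.5: 63.77, so 64 per arm. This reproduces the stated 64.
- One-sided 0.05 at d = 0.5 would need 51 per arm, so the stated figure implies a two-sided test.
- d = 0.3 would need 176 per arm, so the stated figure rests on the top of the range.
- Dropout: 128 / 0.9 = 142.2, so 143 in total. The stated 140 is close to this.

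The calculation covers one confirmatory comparison, in line with {20a}.

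**2. Type I error of the plan as written.** There is one confirmatory test at 5% and all else is labelled exploratory. The confirmatory error rate is 5%.

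**3. Type I error of a fixed sequence, T1 then T2.**
- If there is no effect at T1, any false claim requires a false rejection at T1, which has probability 5%.
- If there is an effect at T1 but none at T2, the only possible false claim is at T2, with probability at most 5%.

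The family-wise rate therefore stays at 5%. T1 is tested exactly as now, so its power is unchanged: 80.1% at d = 0.5 with 64 per arm.

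**4. Chance of confirming both timepoints.** Each test statistic is taken as normal with mean d × √(n/2), n = 64 per arm and critical value 1.960.
- d = 0.5: mean 0.5 × √32 = 2.828; P(Z > 1.960) = Φ(0.868) = 0.807. The exact t-test gives 0.801.
- d = 0.3: mean 0.3 × √32 = 1.697; P(Z > 1.960) = Φ(−0.263) = 0.396.

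At correlation 0 the joint probability is the product: 0.807² = 0.652; 0.807 × 0.396 = 0.320; 0.396² = 0.157. For positive correlation it comes from the bivariate normal distribution. The article does not give the correlation, so 0 to 0.7 is an assumed range.

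| d at T1 / T2 | ρ = 0 | ρ = 0.3 | ρ = 0.5 | ρ = 0.7 |
|---|---|---|---|---|
| 0.5 / 0.5 | 65.2% | 67.7% | 69.7% | 72.2% |
| 0.5 / 0.3 | 32.0% | 35.1% | 37.0% | 38.6% |
| 0.3 / 0.3 | 15.7% | 20.3% | 23.6% | 27.4% |

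The first row assumes that nothing of the effect fades in the three months after training.

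**The case against.** The strongest reply is that nothing here is wrong. One primary comparison with the rest openly exploratory is accepted practice. An objective to assess long-term effects does not promise a confirmatory test of them, and T2 is still estimated with the same model. The expectation in {7} also covers other cognitive and non-cognitive functions, which nobody would ask to be confirmed. The Discussion's own description of the follow-up agrees with {20a}. The sample size was set for one comparison, and the joint success rate is modest if the effect fades. All of this stands, and it makes the point an improvement rather than the correction of an error.

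Three stronger readings are tempting, and the article does not support them:
- A reader might infer that the error rate is inflated because two MoCA timepoints, or many secondary contrasts, are each read at 5%. {20a} does not adopt that reading; it labels those contrasts exploratory.
- A reader might infer that a fixed share of the first objective is beyond reach. The article gives no basis for such a share, and T2 is estimated in any case.
- A reader might infer that the concluding claims depend on T2. The claim about the class of evidence concerns efficacy in general and does not mention follow-up. The phrase "safe intervention to strengthen cognitive functions in this patient group and prevent cognitive decline" stands in a sentence about what training could be, so it expresses a possibility and not a planned claim.

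The reply does not remove one fact: the hypothesis on the primary outcome names the 3-month horizon, {7} does not call that part exploratory, and a test of it is available without spending alpha from T1.

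**Conclusion.** The point holds as a costless improvement and as a mismatch of wording between {7} and {20a}. It is not a statistical error. The present design keeps type I error at 5% but offers no alpha-controlled answer to the long-term MoCA hypothesis.

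What the sequence would yield depends mainly on the effect at T2: from roughly two chances in three of confirming both timepoints in the best case to about one in four or less if d = 0.3 throughout. These figures assume 64 evaluable participants per arm at both visits, a simple two-group comparison with standardised effects inside the range in {14}, and the assumed correlation. They do not credit any gain from adjusting for baseline.

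**What to change.** Before any unblinded comparison, add to {20a} that the MoCA is tested in a fixed sequence. The T1 contrast comes first at two-sided 5%. Only if it is significant is the T2 contrast from the same mixed model tested at two-sided 5%, as the confirmatory test of the long-term effect. All other measures stay exploratory. Name the same timepoints in {7} and {12}.

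The change takes no alpha or power from T1 and needs no extra participants or data. It does alter the confirmatory claim, so it needs a dated amendment and not just an edit. Protocol version 6.0 is dated 26 November 2025 and recruitment was due to finish by the end of 2025, so the time for it is limited; a sequence chosen after seeing results by group would carry no confirmatory weight. One limit should be stated: a delayed effect that appears at T2 without significance at T1 would remain exploratory.

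If the sponsor prefers to keep T2 exploratory, one phrase in {7} saying so is enough.

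In either case the week of T1 should be reconciled, because {20a} places it at week 9 while the control-group description in {11a} and Participant timeline {13} place the post-test at week 7.
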